### Secondary Outcomes

1. Bodily pain and physical function with 36-item Short-Form General Health Survey (SF-36) [44-46]. SF-36 scores range from 0 to 100, with higher scores indicating less severe symptoms.

2. Modified Oswestry Disability Index [46]. The Oswestry Disability Index ranges from 0 to 100, with lower scores indicating less severe symptoms.

### Ethics

The study will be conducted in accordance with the principles outlined by the 18^th ^World Medical Assembly, the Declaration of Helsinki (World Medical Association International Code of Medical Ethics (WMA) General Assembly, Pilanesberg, South Africa, October 2006) and all applicable amendments detailed by the World Medical Assemblies, the ICH (The International Conference on Harmonisation of Technical Requirements for Registration of Pharmaceuticals for Human Use) guidelines for Good Clinical Practice (GCP), and the Medical Research Involving Human Subjects Act of the Swiss Academy of Medical Sciences. This cohort study will be conducted in compliance with all international laws and regulations as well as any applicable guidelines.

### Statistical analysis

Epidemiologic data and patients' descriptive data available on continuous scales will be presented with medians, interquartile ranges or means and standard deviations as appropriate. Categorical data will be presented as rates and percentages. Associations of the continuous independent variables with the outcome variables will be reported using simple logistic regressions. Results from univariate analysis will guide multivariable modeling.

Assessment of associations will be performed using multi-variable models including potential confounders along with the independent variables of interest. Prognostic scores will be built using either logistic regression analysis or Cox proportional hazard models. Models will be validated in subsamples by cross validation. Calibration and discrimination of the cross-validated prognostic instruments will be assessed using the Brier Score.

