There is some evidence from randomized trials [5,16,17] and observational studies [18-22] that surgery improves symptoms in patients with spinal stenosis. The therapeutic effectiveness of conservative measures or surgery, as mentioned in the guidelines of the North American Spine Society, should be evaluated by further randomised controlled trials [1]. Such trials, however, as demonstrated in the study by Weinstein [16], are difficult to execute in patients with spinal stenosis. In the aforementioned study, patients with spinal stenosis were randomly allocated to either surgery or conservative treatment. Two years after randomization, only 67% of patients in the surgical group actually received surgery and 43% of those who were assigned to conservative treatment had also undergone surgery. Physicians and/or patients seem to have strong preferences for surgery or conservative therapy impeding the accomplishment of randomised trials [23].

The long term success rates of surgery vary between 45% and 72%, depending on the measured clinical outcome assessed (pain, walking capacity, neurologic symptoms, working ability) [24]. The outcome of surgery depends on a number of different factors. Indicators of postoperative outcome have been evaluated in different populations and the results have been summarized in a systematic review [25,26]. A lower self rated preoperative health-status, comorbidity, depression and limited, preoperative walking ability are strong predictors of an unfavorable clinical outcome.

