### Study sample size

Sample size is calculated for objective one, the development of a prognostic function for patients undergoing spine surgery, one year after surgery. Outcome after surgery will be quantified by the Swiss Spinal Stenosis Questionnaire (SSM)[28] and results will be dichotomized. An improvement of more than 0.5 points on the symptom severity scale and physical function scale in the SSM will be categorized as improved. According to the original publication [28] 0.5 points represents a clinically relevant improvement for the patients (Minimal Clinical Important Difference). We estimate that 60% of all patients with verified diagnosis will undergo surgery and two thirds of these (between 60% and 70%) of patients will show an improvement of more than 0.5 points in both scales (symptom severity and physical function) one year after surgery. To estimate the effect of ten prognostic variables we need roughly 100 patients without improvement, as defined above, after surgery. This leads us to include 350 patients in the study who undergo surgery.

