### Outcome measures (baseline and follow up)

Primary and secondary outcome data will be collected at baseline and at six weeks and six months after the time of treatment onset (surgery for the surgery group and time of enrolment for the nonsurgical group). Long-term outcome data will be gathered after one year and then annually up to three years.

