### Primary Outcome

The Swiss Spinal Stenosis Questionnaire (SSM)[28] has been recommended by the North American Spine Society (NASS) [1] as the "gold standard" to quantify outcome in patients with spinal stenosis, will be used to quantify outcome. The SSM consists of three different subscales; severity of symptoms (possible range of the score is 1 to 5), physical function characteristics (possible range of scores is 1 to 4) and patient's satisfaction after treatment (the range of the scale is 1 to 4). In the present study, both the severity of symptoms and the physical function scales will represent the primary outcome, whereby a minimum of 0.5-point change in each will be required for the treatment to be considered a success. The SSM has been used as the primary outcome in different studies on lumbar spinal stenosis [39-43] and a German version is available.

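### One-predictor results, which cannot account for baseline SSM, guide the modelling of a change-from-baseline outcome, so adverse predictors that accompany worse baseline scores can be masked

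*Protocol article*

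**What the plan says.** Study sample size defines the outcome: "An improvement of more than 0.5 points on the symptom severity scale and physical function scale in the SSM will be categorized as improved". Primary Outcome puts it as "whereby a minimum of 0.5-point change in each will be required for the treatment to be considered a success". The two differ only for a change of exactly 0.5, which does not matter here; on either wording success is a dichotomised change from baseline. The scales are bounded: "severity of symptoms (possible range of the score is 1 to 5") and "physical function characteristics (possible range of scores is 1 to 4"). The baseline value will be available: "Primary and secondary outcome data will be collected at baseline and at six weeks and six months" after treatment onset.

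Statistical analysis then sets an order of work. First, "Associations of the continuous independent variables with the outcome variables will be reported using simple logistic regressions". Next, "Results from univariate analysis will guide multivariable modeling". The multivariable models are to take in possible confounders as well, but none is named. No section lists the baseline SSM as a predictor, a confounder or a fixed covariate.

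The Background (Treatment modalities) already names likely predictors: "A lower self rated preoperative health-status, comorbidity, depression and limited, preoperative walking ability are strong predictors of an unfavorable clinical outcome".

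**The concern.** With a change-score outcome, the starting value is itself a determinant of success. A patient with a high (poor) score has more room to fall by 0.5 points and also gains from regression to the mean. A factor that travels with poor baseline scores therefore picks up a favourable push in a one-predictor model, which offsets any real adverse effect at equal starting severity.

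The factors most exposed are plausibly those the Background calls strong. Limited walking is close in content to the physical function scale, and depression and poor self-rated health may well accompany worse symptom scores. If such a factor is set aside because its unadjusted result looks neutral, the rule loses information it was built to use. The Discussion says the results should help patients and physicians choose a therapy, so a rule that is silent on a factor that matters at the same starting severity would misinform that choice.

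**Working it through.** **The plan's own figure.** One hundred non-improvers for ten variables implies ten per variable. At 70% success, 100/(1 - 0.70) = 334 patients; conversely 350 x 0.30 = 105. So 350 is a cautious rounding. The point does not depend on it; n = 350 is taken as given.

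**Inputs from the article.** n = 350 surgical patients; two-thirds success; success requires a 0.5-point improvement on both scales.

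**Assumed inputs (none is in the article).** Higher score = worse. Baseline SD 0.65 on both scales; residual SD 0.7; correlation 0.6 between the scales, for baselines and for residuals. Slope b of follow-up on baseline 0.3-0.5; predictor effect g of 0.2-0.3 baseline SD per predictor SD; predictor-baseline correlation r of 0-0.5. No floor.

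**Algebra.** Let X be the predictor in SD units, s the baseline SD and B the centred baseline. Follow-up is F = constant + bB + g·s·X + error, so

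change = B - F = constant + (1 - b)B - g·s·X - error.

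Given B, the slope on X is -g·s. Without B, since E(B | X) = r·s·X, it is [(1 - b)r - g]·s. The unadjusted slope vanishes at r* = g/(1 - b) and changes sign above it. With g = 0.2 and b = 0.5, r* = 0.2/0.5 = 0.40.

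**Simulation.** 500 runs per setting, intercept set for two-thirds success; Monte Carlo standard error of a percentage at most √(0.25/500) = 2.2 points. Cells give the odds ratio for success per SD of X (below 1 is adverse) and the share of runs finding X adverse at p<0.05.

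| g, b | r* | Univariate r=0 | r=0.2 | r=0.3 | r=0.4 | r=0.5 | Adjusted for both baseline scores, r=0.2-0.5 |
|---|---|---|---|---|---|---|---|
| 0.2, 0.3 | 0.29 | 0.76, 66% | 0.92, 10% | 1.02, 2% | 1.12, 0% | 1.24, 0% | 0.71-0.72, 60-71% |
| 0.2, 0.5 | 0.40 | 0.73, 75% | 0.86, 26% | 0.93, 9% | 1.01, 2% | 1.08, 0% | 0.72, 63-74% |
| 0.3, 0.3 | 0.43 | 0.66, 94% | 0.80, 51% | 0.89, 15% | 0.98, 4% | 1.07, 0% | 0.60-0.61, 91-98% |
| 0.3, 0.5 | 0.60 | 0.63, 97% | 0.73, 73% | 0.80, 47% | 0.86, 27% | 0.93, 8% | 0.60-0.61, 93-99% |

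The crossings fall where the algebra puts them. At r = 0.5 the univariate result is significantly favourable, the wrong direction, in 45%, 8%, 9% and 0% of runs (rows in order). A lenient screen does not rescue the predictor: at g = 0.2, b = 0.5, r = 0.4, 9% are found adverse at p<0.20, against 86% with adjustment.

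**Outside that range.** With g = 0.4, b = 0.5, r = 0.3 the univariate odds ratio is 0.69 and 89% are found adverse; with g = 0.5, b = 0.5, r = 0.4, 0.62 and 97%; with g = 0.3, b = 0.7, r = 0.3, 0.72 and 80%. Adjusted odds ratios are 0.52, 0.43 and 0.61: attenuation, but the predictor is usually kept.

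**A second model with scale floors.** Here the assumed baseline means are 3.1 (symptoms) and 2.4 (function), with success about 60% and an effect of 0.2 SD. Success rises from 30% in the best quarter of baseline function to 82% in the worst. At correlations 0, 0.2, 0.4 and 0.5 the simple odds ratio is 0.76, 0.88, 1.07 and 1.17, against adjusted values of 0.70, 0.68, 0.70 and 0.69. The pattern is the same.

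**The case against.** Four arguments on the other side have weight.

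- **The multivariable models may contain baseline SSM.** The article allows for confounders without naming any, and an article may leave the covariate list to a fuller document. This stands: it cannot be said that the final rule omits the baseline score. It does not reach the one-predictor step, which is stated and cannot contain it.
- **No deletion rule is given.** The results are to guide modelling; there is no p-value threshold, and nothing says that factors known from the literature would be discarded. This stands too. Loss of a predictor is a possibility, not a stated consequence.
- **A wrong sign in the final rule is unlikely if baseline SSM is a candidate.** In the assumed settings (correlation 0.3-0.4), at least one baseline score passes a univariate p<0.05 screen in 99-100% of runs, and once it is in the model any other predictor carries its baseline-adjusted sign. What remains is loss at the screening step.
- **An unadjusted odds ratio is not biased in itself.** It correctly describes the marginal association with the defined outcome, and reporting it is harmless. The difficulty is using it to steer a model meant to apply at a given starting severity.

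The size also rests entirely on inputs from outside the article. If the Background's factors are as strong as it says, they may survive the univariate step in weakened form.

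**Conclusion.** The concern holds as a weakness in a stated analysis step. Success is a change from baseline, one-predictor results that cannot adjust for baseline guide the modelling, and the baseline SSM is nowhere named as a covariate. Predictors that accompany worse baseline scores can be attenuated, masked or, at high correlation, reversed at that step, and may then be dropped.

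The size is conditional on the assumed correlation, effect and slope. Masking is substantial in most of the moderate range examined, modest in its most favourable corner (correlation 0.2, effect 0.3, slope 0.5), and small at zero correlation.

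A reader might infer that depression, poor health or limited walking will certainly fall out of the rule or enter it with the wrong sign. The article does not support that: it sets no exclusion threshold, leaves room for baseline SSM among the confounders, and gives no figures from which the correlations or effects could be fixed.

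**What to change.** In Statistical analysis, state that both baseline SSM scores, symptom severity and physical function, stay in every multivariable model for the SSM outcome whatever their p-values. State also that no predictor is dropped on an unadjusted univariate result: either choose the candidates from prior knowledge, starting with the factors in the Background, or let associations adjusted for both baseline scores guide the modelling. Unadjusted odds ratios can still be reported as descriptive.

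No new data are needed, since the SSM is already collected at baseline. The cost is two of the ten variable places, leaving eight for other predictors, unless the unnamed ten already include these scores. If ten others are to be kept, the plan's implied ten per variable gives 12 x 10 = 120 non-improvers: 120/0.40 = 300 surgical patients at 60% success, 120/(1/3) = 360 at two thirds, and 120/0.30 = 400 at 70%, against the 350 planned.

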### Data to be collected

At baseline information about socio-demographic characteristics, symptoms, clinical examination, consumption of analgesics and other treatments for lumbar spinal stenosis within the last 6 months will be collected. Radiological findings (CT, MRI) at different measurement points between lumbar vertebra 1 to lumbar vertebra 5 (central stenosis: antero-posterior diameter of spinal canal, cross sectional area of dural tube, interpedicular distance[29-31]; lateral stenosis: height and depth of the lateral recess [32-35]; foraminal stenosis: foraminal diameter will be quantified [36].

Comorbidities will be assessed with the validated Cumulative illness rating scale (CIRS) [37] which rates the presence and severity of comorbid diseases in 13 organ systems from 0 to 4, and sums organ-specific scores across systems to yield a summary score. Depression, a prognostic indicator, will be quantified with the Hospital Anxiety and Depression Score (HADS). The questionnaire consists of 14 questions, seven for anxiety and seven for depression [38].

Information about treatment will be collected at baseline for six months preceding enrolment in the study and at each follow-up visit for the period between the visits.

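### The sample size is justified for ten prognostic variables, but the analysis lets univariate results shape the model without limiting how many candidates are examined, so the ten-per-variable ratio is not secured

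*Protocol article*

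**What the plan says.** All references are to Methods/Design in the protocol article.

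- **Study sample size** gives the justification: "To estimate the effect of ten prognostic variables we need roughly 100 patients without improvement, as defined above, after surgery". The expected result of surgery is that "two thirds of these (between 60% and 70%) of patients will show an improvement of more than 0.5 points in both scales", and the conclusion is: "This leads us to include 350 patients in the study who undergo surgery". The ten variables are not named.
- **Statistical analysis** describes the route to the model. First, "Associations of the continuous independent variables with the outcome variables will be reported using simple logistic regressions". Then: "Results from univariate analysis will guide multivariable modeling". No threshold, selection rule or candidate number is given. Prognostic scores come from logistic or Cox models, are cross-validated in subsamples and are assessed with the Brier score. Shrinkage is not mentioned.
- **Data to be collected** lists the baseline pool. One part reads: "At baseline information about socio-demographic characteristics, symptoms, clinical examination, consumption of analgesics and other treatments for lumbar spinal stenosis within the last 6 months". Another reads: "Radiological findings (CT, MRI) at different measurement points between lumbar vertebra 1 to lumbar vertebra 5", covering three central, two lateral and one foraminal measure. The CIRS comorbidity score and the HADS (anxiety and depression) are added.
- **Outcome measures**, **Primary Outcome** and **Secondary Outcomes** add baseline values of the SSM symptom and function scales, two SF-36 scales and the Oswestry index.

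**The concern.** The two sections do not fit together. If ten variables are fixed in advance and all are fitted, univariate results have no say in which ones enter. If univariate results do influence entry, the outcome has been used on every variable looked at. The ratio of non-improvers to variables must then be taken over that whole set, not over the variables that remain. The sample size section counts ten, and the analysis section does not hold the count to ten.

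The study's main product is an individual probability of improvement, which the Discussion says should help patients and physicians choose a therapy. Selection on univariate results tends to pick variables whose association is overestimated by chance. The fitted probabilities are then too extreme in new patients, which shows as a calibration slope below 1. Univariate screening can also discard variables that matter only jointly with others.

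**Working it through.** **1. The plan's own figure.** Ten variables × 10 non-improvers per variable = 100, as stated. The factor of ten is implied, not named. Operated patients needed = 100 / non-improvement rate:

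- rate 1/3: 300
- rate 0.30: 334
- rate 0.40: 250

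The planned 350 exceeds all three. An unstated loss allowance would account for it (334/0.95 = 352, or 300/0.85 = 353). At 350 the expected non-improvers are 350 × 0.30 = 105, 350 × 1/3 = 117 or 350 × 0.40 = 140, so 10.5 to 14 per variable for ten variables. For ten candidates the size is adequate by its own rule.

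**2. Size of the named pool.** 6 radiological measures + 1 CIRS + 2 HADS + 2 SSM + 2 SF-36 + 1 Oswestry = 14, counting each radiological measure once whatever the number of levels. Five groups have no item count: socio-demographics, symptoms, clinical examination, analgesics and other prior treatments. At one variable per group, 14 + 5 = 19. The article does not say that all of these are candidates, so the number is an assumption and a range is shown.

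**3. Non-improvers per candidate** = non-improvers / candidates.

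| Candidates | 100 non-improvers | 117 non-improvers |
|---|---|---|
| 10 | 10.0 | 11.7 |
| 15 | 6.7 | 7.8 |
| 19 | 5.3 | 6.2 |
| 20 | 5.0 | 5.8 |
| 30 | 3.3 | 3.9 |

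Keeping ten per candidate would need 200 non-improvers for 20 candidates, i.e. 200/(1/3) = 600 to 200/0.30 = 667 operated patients. For 30 candidates it would need 300 non-improvers, i.e. 900 to 1,000 operated patients.

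**4. What selection could cost.** Logistic simulation: 350 patients, about one third non-improved, five true predictors with log odds ratio 0.30 per SD, 150 runs per setting, evaluated in new patients. Effect sizes and correlations are assumptions. Mean calibration slope (1 = no overfitting):

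| Strategy | Uncorrelated | Correlation 0.2 |
|---|---|---|
| Ten fixed predictors | 0.75 | 0.80 |
| Best 10 of 20 | 0.61 | 0.80 |
| Best 10 of 30 | 0.55 | 0.76 |
| Best 10 of 50 | 0.47 | 0.74 |
| p<0.05 screen of 30 | 0.64 | 0.72 |

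The ten fixed predictors included all five true ones, which favours prespecification.

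**5. Does cross-validation catch it?** For the best 10 of 30, uncorrelated, the AUC in new patients was 0.63. Cross-validated AUC was 0.67 with selection done once outside the folds and 0.62 with selection repeated inside them. At correlation 0.2 the corresponding figures were 0.70, 0.71 and 0.70.

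**The case against.** The strongest reply is that the candidate pool is inferred. Nothing says that everything collected is screened. Radiological measures also establish eligibility, SF-36 and Oswestry are secondary outcomes, and some variables may enter as confounders. The only count in the article is ten. The list of ten and the selection rule may be in a full protocol or SAP that is not shown, and their absence from a journal article is not a fault. The verb is also only that results will guide modelling. This stands as a limit on the size of the problem. It does not remove it, because univariate-guided modelling is a method the article states, not a detail it leaves out.

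A reader might multiply six radiological measures by five levels, arrive at about 40 candidates and 117/40 = 2.9 non-improvers each, and conclude that the ten-per-variable protection does not exist and the rule will be overfitted. The document does not support that. Treating each level as a separate candidate is close to a worst case, and measurements of one kind at adjacent levels are unlikely to be independent. With 40 candidates correlated at 0.5 within each radiological measure and 0.2 among clinical variables (assumed values), a further simulation gave slopes of 0.78 and 0.71 after screening at p<0.05 and p<0.10. Ten fixed predictors gave 0.81 and 0.79. Much of the shortfall from 1 is thus present without any screening.

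Cross-validation is planned and would expose optimism if selection is repeated in each fold. That also stands, but it measures overfitting and does not correct the coefficients.

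**Conclusion.** The point holds as a should-fix. The sample size argument covers ten variables, while the stated analysis does not confine to ten the candidates examined against the outcome. The justification is therefore not secured and the rule is at risk of overfitting.

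How far it falls short rests on assumptions: about 5 to 6 non-improvers per candidate if about 19 are screened, and 3.3 to 3.9 if 30 are. The consequence ranges from almost nothing (best 10 of 20 with correlation 0.2) to substantial (best 10 of 30 uncorrelated). It depends on the number of candidates, their correlation and the threshold, none of which the article states. If no more than ten candidates were ever examined, the stated ratio would stand. Even then, slopes of 0.75 to 0.80 with ten fixed predictors show that shrinkage is worth having at this size.

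**What to change.** Replace the sentence on univariate guidance in Statistical analysis so that univariate results are descriptive only. Before outcome data are seen, fix about ten candidate parameters. A natural start is the four strong predictors named in the Background (self-rated health, comorbidity, depression, walking ability) together with the two baseline SSM scales. Count parameters rather than variables where a variable has several categories. Fit them together with penalised likelihood or bootstrap shrinkage.

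If data-driven selection is kept, four things are needed: state the number of candidates, restate the non-improvers per candidate in Study sample size, repeat the selection inside every cross-validation fold, and apply shrinkage to the final model.

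The cost is analysis-plan wording and agreement on the list, with no additional patients. The small downside is that variables outside the list become exploratory.

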## Abstract

**Background:**

Lumbar spinal stenosis is the most frequent reason for spinal surgery in elderly people. For patients with moderate or severe symptoms different conservative and surgical treatment modalities are recommended, but knowledge about the effectiveness, in particular of the conservative treatments, is scarce. There is some evidence that surgery improves outcome in about two thirds of the patients. The aims of this study are to derive and validate a prognostic prediction aid to estimate the probability of clinically relevant improvement after surgery and to gain more knowledge about the future course of patients treated by conservative treatment modalities.

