**Methods/Design:**

This is a prospective, multi-centre cohort study within four hospitals of Zurich, Switzerland. We will enroll patients with neurogenic claudication and lumbar spinal stenosis verified by Computer Tomography or Magnetic Resonance Imaging. Participating in the study will have no influence on treatment modality. Clinical data, including relevant prognostic data, will be collected at baseline and the Swiss Spinal Stenosis Questionnaire will be used to quantify severity of symptoms, physical function characteristics, and patient's satisfaction after treatment (primary outcome). Data on outcome will be collected 6 weeks, and 6, 12, 24 and 36 months after inclusion in the study. Applying multivariable statistical methods, a prediction rule to estimate the course after surgery will be derived.

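### The univariate results that guide the model are not repeated inside the cross-validation, so reported performance will be optimistic by an amount that grows with the number of candidate predictors

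*Protocol article*

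**What the plan says.** All of the modelling plan is in the Statistical analysis section of the protocol article. Associations of continuous variables with the outcome are to be reported from simple logistic regressions, and then "Results from univariate analysis will guide multivariable modeling". The next paragraph turns to the scores: "Prognostic scores will be built using either logistic regression analysis or Cox proportional hazard models". Validation follows in one sentence, "Models will be validated in subsamples by cross validation", and the performance measure in another: "Calibration and discrimination of the cross-validated prognostic instruments will be assessed using the Brier Score".

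Three other places matter. The Background of the Abstract gives the aim as to "derive and validate a prognostic prediction aid to estimate the probability of clinically relevant improvement after surgery". The Methods/Design part of the Abstract gives the setting: "This is a prospective, multi-centre cohort study within four hospitals of Zurich, Switzerland". The Study sample size section says: "To estimate the effect of ten prognostic variables we need roughly 100 patients without improvement, as defined above, after surgery". The ten variables are not listed anywhere in the article.

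**The concern.** Cross-validation gives a fair estimate only if the patients in the held-out fold had no part in building the model that is tested on them. Choosing predictors is part of building the model. If univariate associations are computed once on the whole cohort and only the coefficients are refitted in each fold, every held-out patient has already influenced which predictors are in the model. Variables that correlate with the outcome by chance in this sample stay in, and they keep appearing to predict in every fold.

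The plain reading of the section leads there. The univariate results are ones to be reported, which suggests whole-cohort analyses. Those results guide the model, and what is cross-validated is the models rather than the process that produced them. Guiding also suggests judgement rather than a rule, and judgement is hard to repeat automatically in each fold.

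What is at stake is the main product of the study. The Discussion says the results should help patients and physicians decide which therapy to choose, so an overstated performance figure would give the prediction aid more weight than it has earned.

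**Working it through.** **1. The plan's own figure.** The sample size section asks for roughly 100 non-improved patients for ten variables, that is about 10 per variable, with 60% to 70% improving after surgery. The number of operated patients needed is 100 / (1 − improvement rate):

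- 60%: 100 / 0.40 = 250
- 65%: 100 / 0.35 = 286
- two thirds: 100 / 0.333 = 300
- 70%: 100 / 0.30 = 334

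The stated 350 is not reproduced exactly. In reverse, 350 operated patients give 350 × 0.40 = 140, 350 × 0.333 = 117 or 350 × 0.30 = 105 non-improved patients (at 60%, two thirds and 70%). All meet the stated need, so 350 is a cautious rounding up and not an error. It is the sample size used below.

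**2. How many candidates could be screened?** The article does not say. The Data to be collected section covers socio-demographic data, symptoms, clinical examination, analgesic use, earlier treatment, a comorbidity score, anxiety and depression scores, and six radiological quantities measured at several points from L1 to L5. If each radiological quantity is taken at 1 to 5 levels (an assumption), imaging alone gives 6 × 1 = 6 to 6 × 5 = 30 candidates. The outcome questionnaires at baseline add more. A range of 10 to 40 candidates was therefore examined.

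**3. Simulation.** From the document: n = 350 and about one third non-improved. Assumptions not in the document: independent normal predictors, five of them true with a log odds ratio of 0.4 per SD, a univariate screen at a fixed p-value, logistic regression on the variables retained, and 10-fold cross-validation with folds formed at random. There were 200 replicates. The true performance of each final model was measured in 5000 new patients from the same population. AUC is added as a measure of discrimination; the plan itself names only the Brier score.

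| Candidates, screen | AUC: screened once / in each fold / new patients | AUC excess (once − new) | Brier: once / in each fold / new | Brier too low by |
|---|---|---|---|---|
| 10, p<0.20 | 0.709 / 0.697 / 0.704 | 0.005 | 0.198 / 0.201 / 0.201 | 0.003 |
| 20, p<0.20 | 0.716 / 0.688 / 0.695 | 0.021 | 0.196 / 0.205 / 0.205 | 0.009 |
| 40, p<0.20 | 0.723 / 0.672 / 0.679 | 0.044 | 0.196 / 0.213 / 0.211 | 0.015 |
| 20, p<0.05 | 0.710 / 0.685 / 0.695 | 0.015 | 0.198 / 0.205 / 0.203 | 0.005 |
| 40, p<0.05 | 0.713 / 0.670 / 0.688 | 0.025 | 0.197 / 0.209 / 0.206 | 0.009 |

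With screening repeated in each fold, the AUC is slightly pessimistic: by 0.007 at p<0.20 and by 0.010 to 0.018 at p<0.05. As an extreme case with no true predictor (p<0.20), screening once gives an AUC of 0.569 with 20 candidates and 0.600 with 40, against a truth of 0.500.

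**4. What the Brier differences mean.** With one third non-improved, a model that gives everyone the average risk scores 1/3 × 2/3 = 0.222. At p<0.20, the apparent gain over that reference against the true gain is:

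- 10 candidates: 0.222 − 0.198 = 0.024 against 0.222 − 0.201 = 0.021
- 20 candidates: 0.222 − 0.196 = 0.026 against 0.222 − 0.205 = 0.017, about 1.5 times
- 40 candidates: 0.222 − 0.196 = 0.026 against 0.222 − 0.211 = 0.011, more than double

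**5. Precision by hospital.** With 105 to 117 non-improved patients spread evenly over four hospitals (an assumption), each has 105 / 4 ≈ 26 to 117 / 4 ≈ 29.

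**The case against.** The strongest reply is that the text is silent rather than wrong. It does not say that screening is done once on all patients, and models could be taken to include the steps that build them. Guiding need not mean a p-value screen. A journal article commonly leaves the number of folds, how they are formed and what is repeated in each to the full plan, and nothing here contradicts nested selection. The only predictor count given is ten, and with ten candidates the bias is negligible. The case without any true predictor fits poorly with the Background, which names strong predictors from a systematic review.

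Much of this stands. Selection on the full data is a reading of the order and wording of the section, not a stated rule, and the missing fold details are no fault in themselves. The case with no true predictor is an extreme and should not be used to size the problem. The ten-candidate result has to be shown beside the others. What does not stand is that the reply removes the point. The sequence as written leads to the biased procedure, the ten variables are not listed, and many more than ten baseline variables are collected. A fixed list of ten would also leave the univariate step little to do.

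A reader might go further and infer that the subsamples are random and mix hospitals, that the hospitals differ in referral and surgical practice, or that cross-validation cannot count as validation. The article supports none of these. It speaks only of subsamples and does not exclude forming them by hospital. It documents no differences in practice between hospitals and sets common eligibility criteria and a common requirement for surgeon experience. Cross-validation is a recognised form of internal validation.

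**Conclusion.** The point holds on the plain reading of the Statistical analysis section: univariate results shape the model, the resulting models are cross-validated, and nothing provides for repeating the selection. On that reading the cross-validated performance is optimistic. With five true predictors and screening at p<0.20, the AUC excess is about 0.005 with 10 candidates, 0.02 with 20 and 0.04 with 40, and the Brier score is too low by about 0.003 to 0.015. A stricter screen at p<0.05 gives smaller excesses. These sizes rest on the assumed number and strength of predictors, their independence and the screening rule, none of which the article gives. The bias would not arise if the full plan already repeats selection in each fold.

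It would be too strong to say that the performance will certainly be materially inflated, or that the aim to "derive and validate a prognostic prediction aid" is unsupported. Cross-validation can support internal validation. Since all data come from the same four hospitals and no other cohort is mentioned, it cannot show how the aid performs elsewhere, and the article does not draw that line. This is a change that should be made because it is cheap and the stated method is weaker than an available one. It is not a flaw that invalidates the study.

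**What to change.** List the candidate predictors before outcome data are examined. Replace the guiding role of the univariate results with a rule that can be programmed, and repeat every data-driven step (screening, selection, cut-points, shrinkage) within each fold or bootstrap sample. Univariate associations can still be reported descriptively.

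Describe the result as internal validation in the four participating hospitals. Leaving out one hospital in turn can be added as a supportive analysis, accepting that about 26 to 29 non-improved patients per hospital will give imprecise estimates.

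The cost is some programming and reported performance that is slightly less favourable. No new data, extra patients or change in care is needed.
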